## Abstract

**Background:**

Approximately 80% of individuals with Parkinson disease (PD) experience impaired balance and mobility, contributing to freezing of gait, an increased risk of falls, and reduced health-related quality of life. Mind-body interventions, such as mindfulness and yoga, may address both motor and nonmotor symptoms by enhancing mind-body coordination and reducing stress, thereby offering a scalable approach to balance rehabilitation in PD.

**Objective:**

This study aims to evaluate the effects and acceptability of Mindfulness Yoga–Practice Awareness through Cognitive-Based Exercise (MY-PACE), a mobile health–delivered, home-based intervention, on balance, mobility, and psychological well-being in individuals with PD and balance impairment.

**Methods:**

This assessor-blinded, 2-arm, randomized waitlist-controlled trial enrolled 132 individuals with PD and balance impairment, randomized to either the MY-PACE group (n=66, 50%) or the control group receiving routine outpatient care (n=66, 50%). The MY-PACE group will complete a 12-week, Zoom-delivered program incorporating mindfulness, yoga, and mindful walking practices. The control group will receive the intervention after study completion. The primary outcome is functional balance, as measured by the Berg Balance Scale. Secondary outcomes include functional mobility, gait patterns, balance confidence, freezing of gait severity, motor symptoms, anxiety and depressive symptoms, cognitive function, mindfulness, health-related quality of life, and fall incidence. Assessments will occur at baseline, 3 months (T1), and 6 months (T2). Data will be analyzed using linear mixed-effects models under the intention-to-treat principle.

**Results:**

Ethics approval was obtained on September 18, 2019. A preliminary feasibility study with 10 participants was conducted between May and June 2020. The full randomized controlled trial was funded in January 2022 by the Early Career Scheme 2021-2022 of the Research Grants Council, Hong Kong. The trial was prospectively registered on December 10, 2021. Recruitment began in April 2022. As of manuscript submission, 132 participants have been enrolled. Data analysis has not yet commenced. The study protocol and statistical analysis plan follow the original prespecified design. The results are expected to be published in 2026.

**Conclusions:**

This trial will evaluate a telehealth-delivered mindful yoga intervention for improving balance and mobility in individuals with PD. By integrating cognitive-based mindful awareness and motor training, MY-PACE targets both motor and nonmotor contributors to balance impairment. If effective, it may represent a scalable intervention for individuals with PD and other populations with mobility limitations.

**Trial Registration:**

Chinese Clinical Trial Registry ChiCTR2100054145; https://tinyurl.com/4j8f8zvn

**International Registered Report Identifier (IRRID):**

DERR1-10.2196/97781

## Introduction

### Background

Parkinson disease (PD) is the second most common neurodegenerative disorder worldwide, affecting approximately 10 million people. With population aging and increased life expectancy, its prevalence is projected to double by 2040 [1]. As PD progresses, functional balance declines, and motor symptoms become increasingly resistant to dopaminergic therapy [2,3]. Balance impairment imposes a substantial burden on individuals with PD, contributing to falls, fall-related injuries and fractures, functional limitations, an increased risk of institutionalization, and mortality [4,5]. Given the high prevalence and serious consequences of balance dysfunction—and the limited effectiveness of pharmacological management—there is an urgent need for complementary, nonpharmacological interventions to improve functional balance in PD [6,7].

Balance impairment in PD arises from a complex and multifactorial pathophysiology involving both motor and nonmotor mechanisms [7]. Motor deficits include disturbed stepping and postural instability, while nonmotor factors, such as cognitive decline, attentional deficits, and anxiety, further compromise balance control [4,7]. Neurophysiological studies indicate that basal ganglia dysfunction disrupts activation of the supplementary motor area, leading to impaired motor preparation and abnormal movement execution [8,9]. In addition, reduced dual-tasking capacity and difficulty shifting attention among motor, cognitive, and limbic networks contribute to instability. Increasingly, researchers and stakeholders—including the UK National Institutes of Health—have emphasized the importance of addressing nonmotor contributors to functional balance [9,10]. Despite this recognition, relatively few rehabilitation approaches integrate both motor and nonmotor targets.

Beyond pharmacotherapy, clinical guidelines recommend professionally led, cueing-based exercise programs to improve balance and gait in PD [11]. For example, physiotherapist-led interventions using rhythmic auditory stimulation, such as metronome cueing, are widely implemented in Western countries, including Belgium and New Zealand [12,13]. These approaches aim to activate premotor cortical regions through external sensory input, thereby bypassing dysfunctional basal ganglia–supplementary motor area circuits to facilitate improved gait patterns. However, the benefits of continuous cueing often diminish over time [14], possibly because gait control reverts from a goal-directed strategy to automatic processing within the impaired basal ganglia network. Furthermore, externally driven cueing systems are difficult to sustain as ambulatory, real-world interventions that support patients across daily contexts. The implementation of professionally supervised programs can also be resource-intensive and costly, limiting accessibility for many individuals with PD. Although such interventions demonstrate short-term improvements, they fail to reach a substantial proportion of patients in need. Importantly, most cueing-based programs primarily target motor skill training, with comparatively limited attention to nonmotor contributors to balance. Modifiable factors, such as cognition and anxiety, play critical roles in postural control and should be addressed concurrently within comprehensive balance rehabilitation strategies.

Mindfulness, a cognitive-based therapeutic approach, cultivates present-moment awareness with openness and nonjudgmental acceptance [15]. A systematic review of neuroimaging studies indicates that mindfulness-based interventions are associated with increased activation in the insula and prefrontal cortex—regions implicated in attentional control and emotional regulation [16]. Emerging empirical evidence further supports the use of mindfulness-based interventions for stress reduction and motor symptom management in PD [17,18]. A 2019 randomized clinical trial (RCT) demonstrated that mindfulness yoga is safe and effective in reducing anxiety and improving motor symptoms in individuals with PD, supporting its role as a complementary therapeutic strategy [17]. A subsequent 3-arm RCT showed that mindfulness techniques, including meditation and yoga, significantly improved anxiety, motor symptoms, and health-related quality of life (HRQOL) compared with usual care, with additional reductions in inflammatory markers [18]. Meditation also demonstrated sustained benefits for depressive symptoms and motor outcomes at a 6-month follow-up. Qualitative findings from this trial indicated that mindful walking improved gait and boosted confidence in balance among participants with PD [19]. Collectively, these findings highlight the multidimensional biopsychosocial benefits of mindfulness-based interventions in PD. Mindfulness techniques may function as an internal cueing strategy by enhancing attentional control, cognitive flexibility, and emotional regulation—mechanisms directly relevant to postural control and balance. Therefore, integrating mindfulness practice with motor skill training may enhance the avenues through which individuals improve mind-body coordination and functional balance.

Building on this evidence, we developed a novel intervention—Mindfulness Yoga–Practice Awareness through Cognitive‑Based Exercise (MY‑PACE). Unlike conventional motor-focused rehabilitation programs, MY‑PACE concurrently targets motor performance, attentional regulation, and anxiety management. The program is designed to enhance participants’ awareness of body coordination, postural alignment, and movement control, while cultivating emotional stability to reduce anxiety-related interference with balance. MY‑PACE incorporates audio‑guided mindful walking to support structured self‑practice, facilitating the development of internal cueing strategies applicable to everyday mobility tasks. By integrating mindfulness training with movement-based exercise, MY‑PACE seeks to engage cognitive, emotional, and motor pathways simultaneously, thereby expanding the mechanisms through which individuals may improve mobility, cognitive control, and emotional regulation to support functional balance.

### Aims and Hypotheses

This study aims to do the following:

Examine the effects of MY‑PACE, compared with usual care, on functional balance (primary outcome) and secondary outcomes, including functional mobility, balance confidence, freezing of gait (FOG) severity, motor symptoms, anxiety and depressive symptoms, cognitive function, mindfulness, HRQOL, and the incidence of falls over a 6‑month period in individuals with PDExplore participants’ experiences with MY‑PACE, including their practice of mindfulness yoga and factors influencing motivation, acceptability, and integration into daily life

It is hypothesized that participants with PD who receive the MY‑PACE intervention will demonstrate significantly greater improvements in functional balance at postintervention follow-up (T1) and at the 6‑month follow‑up (T2) compared with those receiving usual care. In addition, it is hypothesized that participants in the MY‑PACE group will show greater positive changes in secondary physical, psychological, and cognitive outcomes relative to the control group across the same time points.

The exploratory research question is as follows: What are participants’ experiences of using mindfulness yoga as a lifestyle intervention for balance management, particularly regarding perceived effects, perceived mechanisms of action (ie, how and why mindfulness may or may not work), and contextual factors influencing motivation, acceptability, and real‑life practice?

## Methods

### Study Design

This study is a multicenter, assessor-blinded, 2-arm RCT using a sequential explanatory mixed methods design to evaluate the effectiveness and acceptability of a 12-week home-based mindfulness yoga program (MY‑PACE) compared with usual care. The study flow is presented in Figure 1 (CONSORT [Consolidated Standards of Reporting Trials] flow diagram). Outcomes will be assessed at 3 time points over 6 months: baseline prior to randomization (T0), 1 week after intervention (T1), and 3 months after intervention (T2).

**Figure 1 figure1:**
[figure not shown]
CONSORT (Consolidated Standards of Reporting Trials) flow diagram. MY-PACE: Mindfulness Yoga–Practice Awareness through Cognitive-Based Exercise.

To complement the quantitative evaluation, individual semistructured qualitative interviews will be conducted at T1 with a purposive sample of 30 participants from the intervention group. Interviews will explore participants’ experiences with the MY‑PACE program, including perceived benefits, challenges, mechanisms of action, and views regarding the role of mindfulness yoga in managing PD-related symptoms. The sequential explanatory mixed methods design enables a comprehensive assessment of both intervention outcomes and implementation processes [20]. Quantitative analyses will determine the comparative effectiveness of MY‑PACE vs usual care, while qualitative findings will provide contextual insight into participant experiences, perceived mechanisms of change, and factors influencing engagement and adherence. Triangulation of quantitative and qualitative data will enhance understanding of how and why the intervention may influence balance, mobility, and related outcomes. The development-evaluation-implementation process of this study follows the Medical Research Council framework for complex interventions [21].

### Study Participants

Individuals were eligible for inclusion if they (1) had a diagnosis of idiopathic PD (Hoehn and Yahr stage I-III) and reported subjective balance or mobility difficulties [22] (this criterion was selected to capture early functional limitations that are relevant to patients’ perceived mobility challenges and daily functioning; objective measures of balance and mobility were collected at baseline to characterize impairment severity), (2) were aged ≥18 years, (3) were able to ambulate independently with or without an assistive device, (4) were able to provide written informed consent, and (5) had access to a smartphone or tablet device with an internet connection to participate in the online intervention. Individuals were excluded if they (1) were currently participating in another behavioral or pharmacological trial; (2) demonstrated significant cognitive impairment as indicated by the Hong Kong Montreal Cognitive Assessment 5‑minute protocol, using age- and education-adjusted normative cutoff scores [23,24]; or (3) had serious medical conditions other than PD, or any contraindication to mild‑to‑moderate physical exertion that would limit safe participation in the intervention (eg, severe visual or hearing impairment, unstable cardiovascular disease, or significant orthopedic conditions).

### Sample Size Calculation

Taking functional balance as the primary outcome, a meta‑analysis in individuals with PD reported a pooled mean difference of 3.64 (95% CI 2.06-5.22) points for resistance and balance training compared with control, corresponding to an estimated standardized effect size of Cohen *d*=0.66 [25], while a meta-analysis of cognitive-motor training in PD reported a standardized mean difference of 0.58 for balance outcomes compared with active or passive controls [26]. As this study will compare internally cued motor training with usual care, a conservative moderate effect size of 0.55 is assumed for the primary outcome. Using G*Power (version 3.1) for a 2‑arm parallel randomized controlled trial with a 2‑sided significance level of 0.05 and 80% power, 110 participants were required to detect an effect size of 0.55. Allowing for an anticipated attrition rate of 20%, a total sample size of 132 participants (66 per group) was recruited.

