### Procedure

Participants were recruited from local outpatient clinics and community organizations serving individuals with PD, including the Hong Kong Parkinson’s Disease Foundation, the Hong Kong Parkinson’s Disease Association, and the Community Rehabilitation Network. Study information and promotional materials were disseminated through online platforms and organizational networks. Potential participants were contacted by telephone or WhatsApp (Meta Platforms Inc) and screened for eligibility. Eligible individuals received a detailed explanation of the study via videoconference. Written informed consent was obtained in person prior to data collection. Following consent, baseline demographic and clinical assessments were conducted. All outcome assessments were performed during the participants’ self-reported medication “on” state to minimize the influence of motor fluctuations. Assessments were administered by trained research personnel who were blinded to group allocation. Participants were then randomly assigned in a 1:1 ratio to either the MY-PACE group (mindfulness-based, internally cued motor training) or the usual care group using a computer-generated randomization sequence. The allocation sequence was prepared by a researcher not involved in recruitment, intervention delivery, or outcome assessment. Group allocation was communicated to participants by an independent staff member to ensure allocation concealment. All outcome assessors remained blinded to group assignment throughout the study period.

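### The 20% attrition allowance is applied by multiplying, so 132 randomized does not preserve the stated 110; power is barely affected, but the statement needs correcting

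*Protocol article*

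**What the plan says.** All the figures stand in the Sample Size Calculation section of the protocol article. The effect size is fixed first: "a conservative moderate effect size of 0.55 is assumed for the primary outcome". The software and design follow, "Using G*Power (version 3.1) for a 2‑arm parallel randomized controlled trial", with a "2‑sided significance level of 0.05 and 80% power". The result is given as "110 participants were required to detect an effect size of 0.55". The next sentence applies the attrition allowance: "Allowing for an anticipated attrition rate of 20%, a total sample size of 132 participants (66 per group) was recruited". The Procedure section gives equal allocation: "Participants were then randomly assigned in a 1:1 ratio".

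The article shows no inflation formula and does not say which G*Power test was used.

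**The concern.** The article presents 110 as the number needed for the primary outcome and 132 as the number that secures it against 20% attrition. A reader will take both statements together and expect 110 evaluable participants to remain if one in five is lost. On the article's own figures they will not. 132 is what results from adding 20% to 110, whereas losing 20% of those enrolled requires division by 0.80.

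What is at stake is mainly the reliability of a published sample-size statement. If attrition turned out exactly as planned, the results paper would report about 106 completers against a published requirement of 110. That would look like a shortfall the protocol said it had covered. The Limitations section names attrition as a methodological concern, so readers are likely to use the stated tolerance.

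**Working it through.** **Inputs.** From Sample Size Calculation: d = 0.55, two-sided α = 0.05, power 80%, 110 required, attrition 20%, 132 recruited (66 per group). From Procedure: 1:1 allocation.

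**Step 1. Reproduce 132.**
- Multiplying: 110 × (1 + 0.20) = 132. This matches the stated total exactly.
- Dividing: 110 / (1 − 0.20) = 137.5, rounded up to 138 (69 per group).
- Difference: 138 − 132 = 6 participants.

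**Step 2. What 132 delivers.**
- Left after 20% loss: 132 × 0.80 = 105.6, or 52.8 per group.
- Shortfall against 110: 110 − 105.6 = 4.4, that is 4 to 5 participants.
- Largest loss that still leaves 110: 1 − 110/132 = 16.7%.

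**Step 3. Can 110 be reproduced?** The test is not named, so a two-sample t-test is assumed here as the natural reading for a two-arm comparison of means. Power is the probability that a noncentral t variable with n₁ + n₂ − 2 degrees of freedom and noncentrality d·√(n₁n₂/(n₁+n₂)) falls outside the two-sided 5% critical values.

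| Evaluable (per arm) | Power at d = 0.55 |
|---|---|
| 104 (52 + 52) | 79.3% |
| 105 (52 + 53) | 79.7% |
| 105.6 (52.8 + 52.8) | 79.9% |
| 106 (53 + 53) | 80.1% |
| 110 (55 + 55) | 81.6% |
| 132 (66 + 66) | 88.0% |

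The smallest equal-arm total reaching 80% is 106. The normal approximation gives 2(1.960 + 0.842)²/0.55² = 51.9, so 52 per arm or 104.

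Other options at d = 0.55 do not return 110 either:
- t-test, one-sided at 80% power: 84
- t-test, two-sided at 85% power: 122
- t-test, two-sided at 90% power: 142
- ANOVA or ANCOVA with f = 0.275: 106
- Repeated-measures between-group test: 58 to 102 (assuming 2 or 3 measurements and correlations of 0.3 to 0.9)
- Wilcoxon test: 112 with the normal relative efficiency, 124 with the minimum

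**Step 4. Start from 106 and inflate correctly.** 106/0.80 = 132.5, so 133, or 134 with equal arms. The recruited 132 is 1 to 2 below this. Its tolerance for keeping 106 is 1 − 106/132 = 19.7%.

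**The case against.** The strongest reply is that the design claim survives. The section promises 80% power at d = 0.55 with 20% attrition. Under a t-test, 132 randomized delivers 79.7% to 80.1% after that loss, because 110 is above the minimum and absorbs the under-inflation. This stands, and it limits the point to a correction of the text.

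A second reply concerns the 110. A reader might infer that G*Power was run wrongly because the t-test answer is 106. The documents do not support that. The test family is not named, an article may leave that detail to a fuller document, and rounding up from 106 would explain 110, although the text does not say so. Under a t-test 110 gives 81.6%, which errs on the safe side. It is an unexplained but conservative number and not a proven mistake.

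A third reply addresses the inference that the trial has no power in reserve. That would hold only if the full 20% were lost and the analysis were a t-test on completers. With no loss, t-test power is 88.0%. The Data Analysis section plans a linear mixed model that keeps anyone with at least one outcome measurement, so a participant seen after the intervention but lost later still contributes. The article gives no within-person correlation, so this gain cannot be quantified, but it cannot be assumed to be zero.

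None of these replies repairs the attrition step. Reading the 20% as a simple add-on would reproduce 132, but the article calls it an anticipated attrition rate, which is a share of those enrolled.

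**Conclusion.** The attrition step is wrong as written. With 132 randomized, the stated 20% loss leaves about 105 to 106 evaluable participants instead of 110. The total needed to keep 110 would be 138, and 132 covers a loss of 16.7%. This rests only on the article's own figures and on attrition being a proportion of those enrolled.

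The consequence for power is small: about 80% at the planned loss, assuming a two-sample t-test with independent observations at d = 0.55. A reader might infer that the trial is underpowered, but the figures do not show that. The origin of 110 remains unexplained under the natural reading, which calls for a clarification from the authors.

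**What to change.** Restate the attrition sentence without changing enrolment, in one of two ways:
- With 132 randomized, 20% attrition leaves about 106 evaluable participants, which gives about 80% power at d = 0.55 if a two-sample t-test was the basis.
- With 132 randomized, 110 evaluable participants are retained only if attrition does not exceed 16.7%.

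In either case, name the G*Power test or the rounding that gave 110, and show the attrition formula. The authors should supply the test themselves; the t-test used above is an assumption.

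The cost is a few words and a slightly less favourable stated tolerance. Recruitment, allocation and the planned analysis are unaffected. The Results section reports that no outcome analysis has been done, so the correction can be made now without appearing data-driven.

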### Procedure

Participants were recruited from local outpatient clinics and community organizations serving individuals with PD, including the Hong Kong Parkinson’s Disease Foundation, the Hong Kong Parkinson’s Disease Association, and the Community Rehabilitation Network. Study information and promotional materials were disseminated through online platforms and organizational networks. Potential participants were contacted by telephone or WhatsApp (Meta Platforms Inc) and screened for eligibility. Eligible individuals received a detailed explanation of the study via videoconference. Written informed consent was obtained in person prior to data collection. Following consent, baseline demographic and clinical assessments were conducted. All outcome assessments were performed during the participants’ self-reported medication “on” state to minimize the influence of motor fluctuations. Assessments were administered by trained research personnel who were blinded to group allocation. Participants were then randomly assigned in a 1:1 ratio to either the MY-PACE group (mindfulness-based, internally cued motor training) or the usual care group using a computer-generated randomization sequence. The allocation sequence was prepared by a researcher not involved in recruitment, intervention delivery, or outcome assessment. Group allocation was communicated to participants by an independent staff member to ensure allocation concealment. All outcome assessors remained blinded to group assignment throughout the study period.

